**Inclusion**
I. Aged between 18 and 40 years
II. Have IQ score > 80
III. Capable of providing a written informal consent
IV. Able to comprehend and communicate in English
**Exclusion**
I. Pregnancy
II. DSM-5 substance use within the past 6 months
III. Current or past history of acute and/or unstable physical disorders, e.g. hypertension
IV. Current or past history of neurobiological disorders, e.g. traumatic brain injury
V. Significant hearing and visual impairments
VI. Claustrophobia
VII. Presence of comorbidities requiring urgent medical interventions
VIII. Presence of magnetic-sensitive implanted metals and devices in the body, e.g. cardiac pacemakers
IX. Use of benzodiazepines, anticonvulsants, dopaminergic antagonists, and cholinergic antagonists (autistic participants)
X. Presence of psychopathology rather than specific phobia, screened by Personality Assessment Inventory (neurotypical participants)
XI. Presence of diagnosed autism in any related biologically family members (neurotypical participants)

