### Participants

This study aims to enroll a total of 64 participants, comprising 32 adults diagnosed with autism as per fifth edition of the Diagnostic and Statistical Manual of Mental Disorders (DSM-5), without intellectual disability [26]. This diagnosis will be confirmed through clinical assessment and the Autism Diagnostic Observation Schedule-2 (ADOS-2) [27].

It is important to note that our study will encompass autistic participants who have stable co-occurring mental health conditions and medications [28]. Research findings indicate that 70% of young autistic individuals have at least one co-occurring mental health condition [29–31], and almost half of them meet criteria for more than one [30,31]. We believe that excluding individuals with co-occurring mental health conditions and medication use is impractical and would hinder the generalizability of our findings. In addition, given the normative sex differences in plasticity [32], we will recruit at least 11 females, reflecting a higher male:female (2:1) ratio compared to previous ratio of 2.5–3:1 [33].

Autistic participants will primarily be recruited from Adult Neurodevelopmental Services outpatient clinics at CAMH, and CAMH research registry.

For the control group, an additional 32 neurotypical participants will be recruited through the healthy control registry, alongside advertising at local universities and in newspapers. The recruitment process will involve a 1:1 matching strategy, ensuring that for each autistic adult, a corresponding neurotypical counterpart will be sought based on age, sex, and IQ.

All prospective participants, expressing their willingness to take part in this study, will be referred to our research analyst for a detailed discussion about the study’s objectives, protocols, potential risks, and their rights as research participants. Our research team will then assess the participant’s eligibility for inclusion in the study, with the inclusion and exclusion criteria detailed in Table 1. Each participant will be required to provide a written consent at the outset of the study.

**Table 1 pone.0305013.t001:** Inclusion and exclusion criteria.

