### Measurement

#### Baseline clinical assessment

At the outset of the study, we will perform a series of baseline assessments. All participants who meet the inclusion/exclusion criteria will be administered shortened second edition of the Wechsler Abbreviate Scale for intelligence (WASI-II), Edinberg Handedness Inventory (EHI), Adult Repetitive Behavior Questionnaire-2 (ARBQ-2), the Social Responsiveness Scale-2 (SRS-2), and SPQ [24,34–37]. To screen for the presence of general psychopathology in control adults, neurotypical participants will also complete the Personality Assessment Inventory (PAI) [38]. Furthermore, other than participating in ADOS-2, all autistic participants will complete the Ritvo Autism Diagnostic Scale-Revised (RAADS-R) [39].

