#### Statistical analysis

Hypothesis 1: To test this hypothesis, we will employ a linear regression model with CEA ratio (LTP-like plasticity) as dependent variable and study groups (autistic and neurotypical controls) as independent variable. Age, sex, hemisphere of PAS-EEG assessment, IQ and pre-PAS CEA (an index of individual baseline cortical excitability) will enter the model as ‘control’ independent variables. To ensure robustness, a model diagnostic will be conducted through visual inspection of model residuals for lack of normality, heteroscedasticity, linearity and outliers [46] and Cook’s distance [47] will be used to inspect for influential data points. Potential confounding effect of medication use among autistic adults on plasticity will be investigated in a post-hoc sensitivity analysis that will include mediation as an additional control.

Hypothesis 2: We will use a multivariate analysis of variance to test this hypothesis where TR, as dependent variable, is associated with plasticity in the autism group; S1 plasticity, study groups and their interaction will be the main predictors; and sex, age, hemisphere of PAS-EEG assessment and IQ will enter the model as controls. If the interaction between S1 plasticity and study group proves to be significant at confidence level 0.05, the model estimated slopes of S1 within each group will be investigate using graphs.

Hypotheses 3 & 4: In order to study the effect of active vs. sham rTMS on LTP-like plasticity, we will use an analysis of covariance with CEA ratio (LTP-like plasticity) as dependent variable, groups (active and sham rTMS) as fixed factor, and pre-rTMS CEA ratio as covariate. We will count discontinuation of rTMS session and adverse events to assess tolerability.

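### Controls are screened free of psychopathology but autistic adults are not, so the planned Hypothesis 1 coefficient mixes autism with any effect of psychiatric comorbidity

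*Protocol article*

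**What the plan says.** The two groups enter under different psychiatric criteria.

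- **Controls.** Criterion X of the exclusion list in Table 1 reads: "Presence of psychopathology rather than specific phobia, screened by Personality Assessment Inventory (neurotypical participants". The Baseline clinical assessment section gives the instrument and to whom it is given: "To screen for the presence of general psychopathology in control adults, neurotypical participants will also complete the Personality Assessment Inventory (PAI". That section lists no general psychopathology measure for autistic participants.
- **Autistic adults.** The Participants section says that "our study will encompass autistic participants who have stable co-occurring mental health conditions and medications". It supports this with a prevalence figure, "Research findings indicate that 70% of young autistic individuals have at least one co-occurring mental health condition", and with the argument that "excluding individuals with co-occurring mental health conditions and medication use is impractical and would hinder the generalizability of our findings".
- **Matching.** For each autistic adult, "a corresponding neurotypical counterpart will be sought based on age, sex, and IQ".
- **Analysis.** The Hypothesis 1 regression in the Statistical analysis section adjusts for age, sex, assessed hemisphere, IQ and pre-PAS CEA. One further check is named: "Potential confounding effect of medication use among autistic adults on plasticity will be investigated in a post-hoc sensitivity analysis".

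**The concern.** Every participant with a co-occurring condition other than specific phobia falls in the autistic group, by eligibility. Nothing in the matching, the covariates or the extra check distinguishes those participants from autistic adults without such a condition. If a co-occurring condition shifts the response to PAS, the shift is absorbed into the group coefficient. It could inflate an apparent hyper-plasticity or hide a true one.

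The interpretation of Hypothesis 1 is at stake. The Hypotheses section predicts greater plasticity in autism, and the Discussion would use a positive result to name S1 hyper-plasticity as a mechanism of atypical tactile reactivity and a possible biomarker. As selected, the contrast is between autistic adults with whatever co-occurring conditions they have and screened-healthy adults. The between-group comparison of slopes under Hypothesis 2 has the same feature. Hypothesis 3 does not, because active and sham rTMS are randomized within the autistic group.

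**Working it through.** **1. Which parts of the plan touch psychiatric status?**

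| Element | What it covers | Psychiatric status? |
|---|---|---|
| Eligibility | Screened in controls, stable conditions allowed in autistic adults | Creates the difference |
| Matching | Age, sex, IQ | No |
| Hypothesis 1 covariates | Age, sex, hemisphere, IQ, pre-PAS CEA | No |
| Sensitivity analysis | Medication use | Only where medication and condition coincide |

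An unmedicated participant with a co-occurring condition is coded in the medication analysis like an unaffected one. Criterion IX also bars several drug classes in autistic participants, so medication is an incomplete marker of the condition.

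**2. The plan's own power figure.** The power section gives 90% power for 32 + 32 and a difference of 20.6 points, without an SD. The figure therefore cannot be reproduced, only solved backwards. Assuming a two-sided 5% t-test, 90% power needs d = 0.82, that is SD = 20.6 / 0.823 = 25.0 points. This SD serves below only to convert SD units into points.

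**3. Bias in the planned coefficient.** Let p be the share of autistic adults with a co-occurring condition, 0 the share in controls, and δ the shift in CEA ratio due to comorbidity, in SD units. With no autism effect, the expected group difference is p × δ.

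- p = 0.70 is the literature rate that the protocol cites; 0.70 × 32 = 22.4, about 22 of 32.
- δ is not in the documents; 0.2 to 0.8 SD is an assumed range.
- Rejection rates come from simulation: 20,000 trials, 32 v 32, two-sample t-test at two-sided 5%. The documents state 0.05 only for the Hypothesis 2 interaction, so its use here is an assumption.

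| δ (SD) | Bias = 0.70 × δ (SD) | Points at SD 25 | Rejection rate (nominal 5%) |
|---|---|---|---|
| 0.2 | 0.14 | 3.5 | about 8% |
| 0.3 | 0.21 | 5.25 | about 13% |
| 0.5 | 0.35 | 8.75 | about 27% |
| 0.8 | 0.56 | 14.0 | about 56% to 57% |

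With δ = 0.5 SD and another prevalence, p = 0.50 gives a bias of 0.25 SD and about 16% rejection; p = 0.90 gives 0.45 SD and about 42%.

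A shift in the other direction masks an effect: with a true effect of 0.82 SD and δ = −0.5 SD at p = 0.70, the expected difference is 0.82 − 0.35 = 0.47 SD.

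**4. What a supportive analysis could show.** With a comorbidity term in the model and no comorbid controls, the group coefficient rests on autistic adults without comorbidity against controls. At the 70% rate that is about 10 v 32:

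- SE = √(1/10 + 1/32) = √0.131 = 0.36 SD, so the 95% CI is about ± 2.00 × 0.36 = ±0.7 SD.
- The full comparison has SE = √(2/32) = 0.25 SD, about ±0.5 SD.
- For a true effect of 0.82 SD, power falls from 90% to about 61%. With 16 or 22 comorbidity-free autistic adults it would be about 75% or 83%.

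The within-autism contrast of about 22 v 10 has SE = √(1/22 + 1/10) = 0.38 SD, about ±0.76 SD.

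**The case against.** The strongest reply is that admitting co-occurring conditions is a declared and reasoned choice, and that only a condensed article is shown. Sensitivity analyses are often left to the full protocol or SAP. The first objective merely compares autistic adults with neurotypical controls and makes no claim net of comorbidity. The Discussion's mechanism statement is conditional and leans on the association with tactile reactivity as well as on the group contrast.

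Part of this stands. The inclusive sample is defensible and should not be changed. However, generalizability explains why comorbid autistic adults are admitted; it neither explains a stricter screen in controls nor deals with what follows from it. The asymmetry lies in the stated eligibility criteria. The article does describe how Hypothesis 1 handles confounding, and it names medication alone.

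The reply is also right about size. The 70% is a literature figure for young autistic people, not a forecast for this sample. Enrolment requires stable conditions and excludes recent substance use, comorbidities needing urgent intervention and several drug classes, so the rate or severity may be lower. Specific phobia is allowed in controls, so their share is not exactly zero. The largest assumed shift, 0.8 SD, is about as large as the whole effect for which the trial is powered. The simulation uses an unadjusted t-test, whereas the planned model has covariates.

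A reader might infer that this trial cannot separate autism from comorbidity at all. The documents do not support that. It is true of the analysis as planned; a comparison restricted to autistic adults without comorbidity is possible, though imprecise. Nor do they support reading the rejection rates as the trial's false-positive rate, since neither the size nor the direction of a comorbidity effect is given.

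**Conclusion.** The point holds for the analysis as planned: the Hypothesis 1 coefficient estimates autism together with any comorbidity effect, and the medication analysis is not a substitute check.

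The size is open. The range of 0.14 to 0.56 SD, with rejection in about 8% to 57% of trials, rests on three assumptions: 70% v 0% affected, no effect of autism itself, and a comorbidity shift of 0.2 to 0.8 SD. A small shift does little harm; one of 0.5 SD or more would matter for a claim about mechanism.

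It might be tempting to attribute the group difference to autism only if it persists among autistic adults without comorbidity. That would go too far. With about 10 v 32 participants and about 61% power, a true effect could fail such a test by chance, and the restricted group departs from the broad population that the protocol wants to describe. The point is an inexpensive improvement to what Hypothesis 1 can be said to show. It does not invalidate the design.

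**What to change.** Keep the inclusive autistic sample and the primary Hypothesis 1 model, and make three changes.

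1. **Record the variable.** State that co-occurring psychiatric diagnosis (present or absent) is recorded for each autistic participant when eligibility is assessed. The baseline section does not list this, although admitting people with stable conditions implies that someone ascertains them.
2. **Add a supportive analysis.** In the Statistical analysis section, beside the medication analysis, pre-specify for Hypothesis 1 (a) the difference in CEA ratio between autistic adults without comorbidity and controls, and (b) the CEA ratio in autistic adults with v without comorbidity. Report each with a 95% CI and without a significance gate.
3. **Word the interpretation.** Describe Hypothesis 1 as a contrast of autistic adults, including their co-occurring conditions, with screened-healthy controls. Limit the mechanism statement in the Discussion in light of (a) and (b).

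The cost is one recorded item and one extra analysis; sample size, randomization and procedures are unchanged. The drawback is imprecision: at the 70% rate (a) rests on about 10 autistic adults, with an interval of about ±0.7 SD, so it can only support or temper the main result.

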### Measurement

#### Baseline clinical assessment

At the outset of the study, we will perform a series of baseline assessments. All participants who meet the inclusion/exclusion criteria will be administered shortened second edition of the Wechsler Abbreviate Scale for intelligence (WASI-II), Edinberg Handedness Inventory (EHI), Adult Repetitive Behavior Questionnaire-2 (ARBQ-2), the Social Responsiveness Scale-2 (SRS-2), and SPQ [24,34–37]. To screen for the presence of general psychopathology in control adults, neurotypical participants will also complete the Personality Assessment Inventory (PAI) [38]. Furthermore, other than participating in ADOS-2, all autistic participants will complete the Ritvo Autism Diagnostic Scale-Revised (RAADS-R) [39].

**Phase I. Assessment of plasticity**
*Transcranial Magnetic Stimulation*. TMS procedures will be performed using a Magstim 200 stimulator (Magstim Co., Whitland, UK) equipped with a 70-mm figure-of-eight coil. To enable neuronavigated TMS, structural T1-weighted magnetic resonance (MR) images will be obtained prior to the TMS session. These images will be acquired with a 3T MRI scanner (Discovery **MR750, GE** Healthcare, Chicago, IL, USA) for each participant at the Research Imaging Centre, CAMH. Subsequently, these MR images will be imported into BrainSight software (Rogue, Research Inc, Canada) for individual MRI-guided navigated TMS (nTMS).

The TMS stimulation session will begin with the identification of the cortical representation of the abductor pollicis brevis (APB) muscle, a process known as ‘hotspotting’. To locate the APB hotspot, we will position the intersection of the coil tangentially to the participants’ skull, optimizing it around the C3 electrode (the approximate location of the primary motor cortex for the hand). The coil’s handle will be oriented backward, forming a **45° angle** with the midline. Once the hotspot will be located, we will determine the resting motor threshold (RMT). The RMT will be identified as the lowest stimulus intensity required to induce MEPs with a peak-to-peak amplitude of at least 50 microvolts (μV) in the relaxed right APB muscle, in at least half of 10 consecutive trials. Subsequently, the stimulation intensity is set to 1 mV, i.e. the intensity of TMS required to produce MEPs with a mean peak-to-peak amplitude of 1 mV across 20 TMS trials. 1 mV MEP is typically obtained with a stimulator intensity of 120% of the RMT, and stimulation intensities below this level are generally inadequate for reaching depths greater than 2 cm beneath the scalp. Therefore, we initially set the stimulation intensity to 120% of RMT and then adjust it to achieve the target 1 mV amplitude (SI1_mV_). TMS stimulation will be then applied to the left S1 site (MNI coordinates: X = -48 mm, Y = -21 mm, Z = 50 mm), with the intensity set at SI1_mV_ throughout the session. The orientation of the coil is adjusted to minimize artifacts, specifically aiming to keep observed decay artifacts within 10 ms following TMS pulses to ensure that early evoked responses remain unaffected. This adjustment may cause a shift of the stimulation site within a range of ±1 mm. In total, 100 single pulses will be delivered, with an inter-stimulus interval (ISI) of 5 s. This paradigm will be administered both before and after the PAS intervention at different time points (0, 15, 30, and 60 minutes) (Fig 2A).

**Fig 2 pone.0305013.g002:**
[figure not shown]
Schematic figure of plasticity assessment and intervention phases of the current study. (**A**). The plasticity assessment procedure consists of delivering 100 single TMS pulses over the left S1 using SI1 mV which will be applied before and after (0, 15, 30, and 60 min) PAS intervention. Throughout the PAS intervention, electrical stimulation of the right median nerve will precede TMS stimulation of the left S1 at an ISI of 20 ms. The plasticity will be then assessed using the ratio of the maximum CEA following PAS to the baseline CEA. CEA is quantified as the area under the curve of rectified TMS-EEG response within a time window of 25–275 ms from TMS stimulus onset. (**B**). Autistic participants will be further randomized to receive either a single session sham or active 20 Hz rTMS. The rTMS intervention will be delivered bilaterally over the S1 consisting of 120 trains of 50 pulses with an ITI of 30s (in total, 6000 pulses). The sequence of delivery will be randomized for each participant, that is left S1 followed by right S1 and vice versa, and the pulses will be applied at an intensity of 90% RMT. Following rTMS, on the same day, TMS-EEG plasticity assessment paradigm will be applied.

Participants will remain seated in a comfortable chair for the entire session, and to mask the auditory stimulation from TMS, white noise will be played through earplugs. The volume of the white noise will be carefully calibrated to effectively mask TMS-related sounds while staying within the participant’s comfort limits. The volume, will be gradually increased, monitoring the participant’s comfort level to find the maximum volume that is both comfortable and effective in masking the TMS clicks. Additionally, a layer of foam will be placed on the coil. This combination of foam and adapted white noise has been shown to achieve the greatest reduction in auditory evoked responses associated with the clicking sound of TMS [40].

*Electroencephalographic Recording and Preprocessing*. EEG recordings will be continuously acquired concurrently with TMS using a TMS-compatible 64-channel amplifier (Compumedic Inc) while the electrode impedances will be kept below 5 kΩ. In our EEG recording setup, the reference and ground electrodes are integrated into the EEG cap, with the reference electrode positioned posterior to the CZ electrode and the ground electrode located posterior to the FPZ electrode. An electrooculogram (EOG) electrode is placed under the left eye to record the vertical eye movements. The sampling rate of 20 kHz and a low-pass filter of 100 Hz will be selected, to minimize the artifacts introduced by TMS and avoid amplifier saturation [41].

Thereafter, the acquired EEG data will be preprocessed offline using customized scripts in MATLAB (MathWorks Inc., Natick, MA, USA) and EEGLAB open source MATLAB toolbox, in accordance with a defined cleaning pipeline. According to this pipeline, the EEG data will be (1) trimmed from -2 ms to 10 ms after TMS pulse; (2) decay artifact will be removed with ICA and then data will be down-sampled to 1 kHz; (3) segmented into epochs (-1000 ms to 1000 ms with respect to the TMS pulses); (4) baseline-corrected using the artifact-free pre-TMS interval (from -500 ms to -5 ms); (5) another round of ICA will be applied to remove residual artifacts such as EOG and muscle artifacts. In the last step, data will be filtered using a zero-phase shift band-pass filter with a frequency range of 1 to 100 Hz and 60 re-referenced using an average reference for further analysis.

*Paired Associative Stimulation Intervention*. To induce plasticity in the S1, a PAS paradigm will be adopted. During this PAS paradigm, one hundred eighty electrical stimuli will be delivered peripherally at 0.1 Hz over the right median nerve. The intensity of these stimuli will be set to three times the participant’s perceptual threshold, which is the minimum intensity at which they can perceive the stimulation. To generate an LTP-like plasticity effect, the peripheral stimulation of the median nerve will be preceded the TMS stimulation of the contralateral S1 by 20 ms (Fig 2A). The 20 ms interval will be employed to ensure that the timing of the peripheral nerve stimulation and TMS is aligned with the arrival of the peripheral sensory input in the S1 [42]. Participants will be instructed to maintain their attention on their stimulated wrist and count the number of pulses they will receive throughout the protocol. This instruction is based on the recognition that attention can modulate the effects of PAS, as suggested by the study conducted by Stefan et al [43].

**Phase II. Repetitive transcranial magnetic stimulation procedure in autistic participants** Stimulation will be conducted with an X100 stimulator with a double-sided B65 A/P type fluid-cooled coil (MagVenture, Farum, Denmark Inc.) which is a combined active/sham coil with identical sides. Single-session 20 Hz rTMS will be delivered bilaterally over the S1 at 90% of RMT, with 120 trains of 50 pulses and an inter-train interval (ITI) of 30 s (Fig 2B) (15). In total, 6000 pulses will be administered to each autistic participant. The sequence of delivery will be randomized for each participant, i.e., left S1 followed by the right S1 (MNI coordinates: X = 48 mm, Y = -21 mm, Z = 50 mm) or vice versa. Sham stimulation will be delivered using the sham side of the coil, which does not generate a magnetic field but mimics the sensation of magnetic stimulation and produces the same clicking sounds. We opted not to use electrical scalp stimulation for the sham condition due to the anatomical location of S1, where effective attachment of electrodes cannot be achieved, preventing the production of discernible sensations.

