## Method

### Design and setting

The current study, comprising two phases (Fig 1), one of which is randomized and double-blind, will be conducted at CAMH’s Temerty Centre for Therapeutic Brain Intervention, Toronto, Canada, from April 2023 to April 2025. The authors assert that all procedures contributing to this work comply with the ethical standards of the relevant national and institutional committees on human experimentation and with the Helsinki Declaration of 1975, as revised in 2013. All procedures involving human subjects were reviewed and approved by the research ethics board at CAMH (135/2019).

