**Fig 1 pone.0305013.g001:**
[figure not shown]
Schematic diagram of the study design. Initially, all participants (*N* = 64) will undergo a baseline clinical assessment and MRI brain scan. In their third visit, the participants will complete the SPQ questionnaire and the plasticity in the left S1 will be assessed using PAS-EEG. Only autistic participants will be further randomly assigned to either the active or sham group, in a double-blind manner, to receive bilateral rTMS over the S1, and the plasticity of the left S1 will be reassessed on the same day following rTMS. This session will be scheduled at least one week after the third visit. WASI-II, Wechsler Abbreviate Scale for intelligence—second edition; EHI, Edinberg Handedness Inventory; Edinberg Handedness Inventory (ARBQ-2); Social Responsiveness Scale-2 (SRS-2); Ritvo Autism Diagnostic Scale-Revised (RAADS-R); Autism Diagnostic Observation Schedule—second edition (ADOS-2); MRI: Magnetic resonance imaging; SPQ: Sensory Perception Quotient; PAS: Paired associative stimulation; EEG: Electroencephalography; S1: Primary sensory cortex; rTMS: Repetitive transcranial magnetic stimulation.

All participants, both autistic and neurotypical, will undergo clinical assessments, which include diagnosis confirmation, handedness determination, IQ evaluation, and a TMS safety screen. Additionally, they will undergo a magnetic resonance imaging (MRI) scan of the brain, which will be used for MRI-guided neuronavigated TMS in subsequent sessions. On their next visit, all participants will complete the 92-item Sensory perception Quotient to assess TR [24]. Then, plasticity will be assessed in the left S1 using PAS-EEG paradigm.

Upon completing the first phase, only autistic participants will be randomly assigned in a double-blind manner (1:1) to receive either a single-session of active or sham bilateral rTMS over the S1, followed by PAS-EEG plasticity assessment session, on the same day. Assignment will be determined using a permuted block randomization method [25] generated by an independent biostatistician external to the project. The participants and investigators involved in the study will remain blinded throughout the study, i.e. experiment and data analysis. The investigators will be unblinded only after the analysis of data is completed.

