**Outcomes**
*Primary Outcome*. The primary outcome measure of this study is the PAS-induced LTP-like plasticity in the S1. PAS-induced LTP-like plasticity will be assessed using CEA. CEA is quantified as the area under the curve of rectified TMS-EEG response within a time window of 25–275 ms from TMS stimulus onset [44]. This chosen time window is designed to exclude any early artifacts and account for the subsiding effects of TMS. CEA will be averaged across 100 epochs from the electrodes of interest corresponding to the S1 region. The mean post-PAS CEA will be then divided by the pre-PAS CEA, reflecting the potentiation of CEA at each of post-PAS time points (0, 15, 30, and 60 minutes). Given that the timing of the post-PAS maximum potentiation could differ among participants, we will use the maximum CEA ratio for each participant for the statistical analysis [21].

To asses TR, the total score on the “touch” category of SPQ questionnaire will be used.

**A *Priori* power calculation** A sample size of *N* = 64 participants, consisting of 32 autistic participants and 32 neurotypical controls, has been determined as adequate for hypothesis testing. This sample size provides 90% power. This calculation is based on the preliminary data, the observed LTP-like plasticity difference of 20.6 points [15], as evidenced in our PAS-EEG pilot study involving both autistic adults and control subjects. Moreover, the same sample size is deemed suitable for evaluating hypotheses 2, offering an 80% statistical power to detect a moderate effect size (Cohen’s f2 = 0.15). These power calculations were executed using G*Power [45].

Drawing upon our previously published findings [15], we envision a "substantial" impact of active rTMS in a group of 16 autistic participants when compared to a sham group also consisting of 16 autistic participants. It is important to note that, given the relatively small sample size, the application of a single session, and the exploratory nature of this outcome, our approach to presenting results and their interpretation will extend beyond statistical significance values. Instead, we will place significant emphasis on estimated effects and their precision, including the calculation of 95% confidence intervals. This comprehensive set of information, combined with data related to tolerability, will play a pivotal role in shaping the design of future clinical trials.

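### The stated blinding concerns the rTMS assignment only; nothing masks diagnosis or pre/post-PAS block during the ICA cleaning that produces the primary autistic-versus-control outcome

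*Protocol article*

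**What the plan says.** Under Design and setting, the study is described as "comprising two phases (Fig 1), one of which is randomized and double-blind". After Phase I, "only autistic participants will be randomly assigned in a double-blind manner (1:1) to receive either a single-session of active or sham bilateral rTMS". The article then describes the permuted-block list for that assignment, and directly afterwards states: "The participants and investigators involved in the study will remain blinded throughout the study, i.e. experiment and data analysis".

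Electroencephalographic Recording and Preprocessing says the data are "preprocessed offline using customized scripts in MATLAB" and EEGLAB according to a set pipeline. Two of its steps remove signal by ICA. In step 2, "decay artifact will be removed with ICA and then data will be down-sampled to 1 kHz"; in step 5, "another round of ICA will be applied to remove residual artifacts such as EOG and muscle artifacts".

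Under Outcomes, "The primary outcome measure of this study is the PAS-induced LTP-like plasticity in the S1". It is measured by dividing the CEA at each of four post-PAS times by the pre-PAS CEA, and "we will use the maximum CEA ratio for each participant for the statistical analysis". Under Statistical analysis, Hypothesis 1 regresses this ratio on diagnostic group, with pre-PAS CEA among the covariates.

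**The concern.** Hypothesis 1 compares groups whose membership the team knows: it confirms the autism diagnosis and then seeks a matched control for each autistic participant. Phase I has no random allocation to conceal, so a blinding statement tied to allocation gives this comparison no protection. The outcome nevertheless passes through two steps in which components are classed as artifact and discarded. If judgement enters there, and the person judging knows the diagnosis, cleaning can differ between groups.

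The expected direction is known. Hypothesis 1 predicts greater plasticity in the autistic group, and the Introduction reports that the same team has already found this in motor cortex. The planned residual plots and Cook's distance would not reveal a cleaning difference that runs systematically between groups. Because pre-PAS CEA is also a covariate, the same cleaning affects both sides of the model.

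**Working it through.** **1. Scope of the blinding.** Three statements have to be read together: only one of the two phases is double-blind; the double-blind assignment is to active or sham rTMS and involves autistic participants only; and the sentence on blinding in experiment and analysis follows directly on that assignment. Read this way, what is hidden is the rTMS arm. Diagnosis and pre/post-PAS block are not mentioned. Hypothesis 3 (active versus sham) is covered; Hypothesis 1 is not.

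**2. Where judgement could enter.** The pipeline gives numerical settings for trimming, epoch length, baseline interval and filter band. For the two ICA steps it gives no rule for rejecting a component and does not say who or what decides. The targets in step 5 are given as examples, not as a closed list.

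**3. How cleaning reaches the outcome.** Write the outcome as R = (largest post-PAS CEA) / (pre-PAS CEA). If cleaning lowers pre-PAS CEA by a fraction a, and all post-PAS CEAs by a fraction b, then R becomes R × (1 − b)/(1 − a).
- If a = b, as when blocks are decomposed together and a rejected component takes the same share of CEA from each, R is unchanged.
- If a and b differ but are the same in both groups, both group means are multiplied by the same factor k and their difference becomes k × (difference). A true difference of zero stays zero. Knowing the block but not the diagnosis therefore largely cancels in Hypothesis 1.
- Only cleaning that differs by diagnosis creates a group difference where there is none.

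**4. The plan's own figure.** The A Priori power calculation gives 90% power for 32 versus 32 and a difference of 20.6 points, without SD, alpha or sidedness, so it cannot be reproduced. Assuming two-sided alpha of 0.05 and the normal approximation, the standard error must be 20.6 / (1.960 + 1.282) = 6.355. With SE = SD × √(2/32) = SD × 0.25, the implied SD is about 25.4. At one-sided 0.05 it would be about 28.

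**5. Illustration of sensitivity.** Take SD 25.4, no true difference, and a between-group cleaning bias of B points. The rejection probability of a two-sided 5% test is Φ(B/6.355 − 1.960) + Φ(−B/6.355 − 1.960).

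| Assumed bias B (points) | B / SE | Chance of a false positive |
|---|---|---|
| 0 | 0 | 5.0% |
| 2 | 0.31 | 6.1% |
| 5 | 0.79 | 12.3% |
| 10 | 1.57 | 35.0% |

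The values of B are assumptions. The article gives no size for such a bias, and the table does not estimate one.

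**The case against.** The strongest reply is that this is silence in a condensed article. Nothing says that the operator knows the diagnosis, the scripted pipeline points to fuller detail elsewhere, and file coding or component rules often sit in an operating procedure. Part of that stands: a fuller protocol may contain masking, and a fully automatic preset rule would largely remove the concern. It does not dispose of the point, because the article does define the scope of its blinding, and that scope leaves out the primary comparison.

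A reader might infer more than this, and the document does not support it:
- That a person picks components by eye, block by block. Neither manual selection nor separate decomposition of pre- and post-PAS recordings is stated.
- That one over-cleaned block shifts the result by an amount comparable with the 20.6-point target. A shift in one participant's ratio is not a shift in a group mean; it would have to recur in the same direction across most of one group and not the other. For a post-PAS block, taking the maximum of four ratios also limits any fall, because the next-highest block takes over.
- That knowing the time point is as serious as knowing the diagnosis. On its own it largely cancels between groups.
- That the broad blinding sentence already covers Hypothesis 1. Its wording is wide, but its position and the one-phase statement tie it to the rTMS assignment.

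**Conclusion.** The concern holds as an avoidable risk of observer bias in the primary comparison, not as a demonstrated error. It rests on two things that the article states (blinding tied to the Phase II assignment, and two ICA removals upstream of the primary outcome) and one that it does not (any masking of diagnosis or block during cleaning). Its size is unknown, and would be close to nil if rejection is automatic and identical for all recordings. The false-positive figures show only how sensitive the test would be under an assumed SD of 25.4 and assumed biases. The point deserves action because masking changes how the primary outcome is produced, at little cost. It has no bearing on the sample size.

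**What to change.** Extend the blinding statement to EEG preprocessing. Have a team member who does not do the cleaning code every recording, so that both ICA removals are carried out without knowledge of diagnosis, visit, rTMS arm or pre/post-PAS block. Visit needs coding too: only autistic participants have a second PAS-EEG session, so a visit label can reveal the diagnosis. Alternatively, state a preset automatic rejection rule applied identically to all recordings. In either case, report the number of components removed at each ICA step by group and block.

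The cost is minor file handling and one descriptive table. Preprocessing is offline, so recordings already made but not yet cleaned can be coded as well. Procedures, sample size and the regression model are unchanged.
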